### Eligibility criteria and exclusion criteria

2.4

The included patients are in accordance with the following eligibility criteria: participants meet the diagnostic criteria for PFP; participants have their first onset and the course of disease is within 3 months; participants have unilateral facial muscle paralysis; participants are aged between 15 and 70 years; participants offer informed consent and volunteered to participate in the trial.

Participants meet with these exclusion criteria and are excluded: FP of patient is secondary to other diseases, such as Gillan-Barre syndrome, otogenic facial neuritis (such as otitis media, labyrinthitis, mastoiditis, mumps, and so on), posterior cranial fossa tumors, and meningitis; patients with severe primary diseases such as diabetes, cardiovascular and cerebrovascular disease, liver disease, kidney disease, and patients with mental illness; patients with Hunt syndrome; patients who are younger than 15 years or older than 70 years, women that are pregnant or in lactating.

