### Acupuncture treatment protocol

2.5

All the patients receive acupuncture treatments 5 times/week for a total of 20 sessions over 4 weeks. In the acupuncture treatment, 14 main acupoints are used (acupoints of Yangbai, Zanzhu, Sizhukong, Sibai, Xiaguan, Yingxiang, Dicang, Jiache, Qianzheng, Yifeng on the affected side, and acupoints of Hegu, Taichong on both sides). Minor points can be added and subtracted according to different syndrome differentiation, physique and symptoms, for example, Lianquan is added when taste sense of the front two-thirds of the tongue is loss.

In addition, there is difference in the operation of acupuncture. Acupuncture operation in the acute phase should be light and shallow, without twisting and lifting, and electroacupuncture is forbidden, whereas mild-reinforcing and mild-reducing method is usually used in acupuncture of the recovery period. Electroacupuncture can be chosen for patients with facial muscle atrophy, two pairs of points including Xiaguan-Juliao and Jiache-Dicang are generally chosen and the time is last for 30 minutes. During the period of electroacupuncture, continuous waves are used, with a frequency of 1 to 2 Hz and the output intensity is based on the slight contraction of facial muscles.

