### Surface blood flow signal collection of face

2.6

PeriCam PSI laser speckle imager (Perimed, Sweden) is applied for surface blood flow signal collection of face. The parameter is set as followings: high resolution, 10 images/s of frequency, the acquisition frequency is 50 Hz, and the sampling density is medium. After that, facial blood perfusion volume is recorded over 3 periods: 5 minutes that the patient lies flat and quietly; the whole process of acupuncture; 5 minutes after needle removal. The evaluation criteria for FP in LASCA are shown in Table 4. When monitoring, the patient is in a supine position, facing directly above, and the laser emission and monitoring head are placed about 25 to 30 cm directly above the patient's face.

**Table 4 T4:** Evaluation criteria for facial paralysis in LASCA.

1. ROI: In machine vision and image processing, machine learning and image segmentation methods are used to automatically divide the facial blood flow image into 6 regions: left and right eye area, left and right cheek area, and left and right jaw area.
2. TOI: In machine vision and image processing, periods of interest are selected. Generally, 3 periods are taken: before acupuncture (5 min), during acupuncture (20 min), after acupuncture (5 min).
3. Pr: Pr = P1 (average blood perfusion volume on the healthy side)/P2 (average blood perfusion volume on the affected side). The closer Pr is to 1, the faster the recovery, the better the curative effect, and the better the prognosis.

LASCA = laser speckle contrast analysis.

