### Nerve electromyogram signal collection using H-B rating scale

2.7

Viking Quest EMG system (Thermo Nicolet Corporation, America) is utilized for nerve electromyogram (EGM) signal collection, and room temperature is maintained at 18°C to 25°C. When the patient is performed with BR of facial nerve, we choose a repetitive waveform to measure the shortest latency of R1 and R2 (Table 5). After that facial nerve function before and after acupuncture intervention is assessed by using H-B rating scale (Table 6).

**Table 5 T5:** Evaluation criteria for facial paralysis in BR.

1. The latency of R1 is 10.0 ± 0.6 ms, when the latency of R1 is ≥2 ms and the difference between the latency of bilateral R1 is ≥2.0 ms, these data can be judged as abnormal.
2. The latency of R2 is 29.3 ± 1.8 ms, and the latency that ≥34 ms can be judged as abnormal.
3. Undetectable or absent signal of R1, R2, and contralateral R2 ′is considered as abnormal.

BR = blink reflex.

**Table 6 T6:** H-B rating scale.

1. Mild: H-B rating scale has a local score of II
2. Moderate: H-B rating scale has a local score of III-IV
3. Moderate to severe: H-B rating scale has a local score of V
4. Severe: H-B rating scale has a local score of VI

H-B = House-Brakmann.

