### Statistical analysis

2.9

SPSS 20.0 statistical software is used for statistical analysis of data (SPSS Inc, Chicago, IL). The correlation between H-B score, BR, and Pr would be analyzed by correlation analysis, the closer the correlation coefficient is to 1 or −1, the stronger the correlation, the closer the correlation coefficient to 0, the weaker the correlation. Radit analysis is adopted to analyze H-B facial nerve function rating scale. In terms of surface blood perfusion signal analysis, statistical analysis is mainly performed on Pr values before and after treatment. Data are expressed as “mean ± SD” and homologous paired sample t test is utilized. COX regression analysis is used to analyze the development of FP and the prediction on model of its prognosis and outcomes. *P* < .05 indicates that the difference is statistically significant, as well as *P* < .01 means that the statistical significance is remarkable.

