
### Establishment of predictive model for prognosis of FP based on LASCA technology and research on rehabilitation training mechanism

3.2

The researchers automatically segregate 3 areas of the eyelid, cheek, and jaw of the affected and healthy side of the patient's facial blood flow image are by machine learning methods and synchronize them. At the same time, the common FP assessment method is incorporated into a unified mathematical statistical model, and the law of change in LASCA symmetry value Pr and the development, evolution, and prognosis of FP is observed. The relevant characteristic signals are extracted, and a COX regression analysis method was adopted to establish a highly accurate prediction model for the prognosis of FP based on LASCA technology, and cross-validation is performed.

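### Cox regression is the named prognostic model, but the outcome readings described, before and after a fixed 4-week course, contain no patient-specific event times

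*Protocol article*

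**What the plan says.** Section 2.9 assigns the prognostic question to one method: "COX regression analysis is used to analyze the development of FP and the prediction on model of its prognosis and outcomes". Section 3.2 says that "a COX regression analysis method was adopted to establish a highly accurate prediction model for the prognosis of FP based on LASCA technology", with cross-validation. The Abstract says the same, and no other prognostic model is named.

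On what is measured and when:

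- Section 2.7: "facial nerve function before and after acupuncture intervention is assessed by using H-B rating scale".
- Section 2.9, for the blood-flow ratio Pr: "statistical analysis is mainly performed on Pr values before and after treatment", using a paired t test.
- Section 2.5: "All the patients receive acupuncture treatments 5 times/week for a total of 20 sessions over 4 weeks".
- Section 2.6: "facial blood perfusion volume is recorded over 3 periods". Table 4 gives these as 5, 20 and 5 minutes, so they lie within one session and are not follow-up visits.
- Section 2.4: "participants have their first onset and the course of disease is within 3 months".

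Table 6 groups H-B grades II to VI. It lists no recovered category that could serve as the event.

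**The concern.** A Cox model takes its information from the order in which patients reach an event. That order needs a time that differs between patients because their disease course differs. One reading at the end of a course of common length says whether a patient has recovered by then, not when.

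Two clocks could be used, and neither supplies the missing times. From treatment start, everyone has about the same time, so all events tie in one risk set. From onset, the time is the delay before enrolment plus the course length, so the ordering is set by when the patient enrolled.

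The prognostic model is one of the article's announced products, and the claim made for it is high accuracy. Cross-validation would not repair it, because every fold would have the same empty time axis.

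**Working it through.** **Inputs from the document.** n = 200 (2.2); course of 4 weeks = 28 days for all (2.5); entry up to 3 months after onset (2.4); outcome read before and after (2.7, 2.9). The article gives no recovery rate, effect size or tie rule, so those below are assumptions. The stated sample size cannot be reproduced from the article and does not bear on this point.

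**Simulation.** 300 replicates of 200 patients, one standard-normal baseline predictor, exponential recovery times with a known hazard ratio (HR) per SD, and status read once at day 28.

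*Clock 1: time from treatment start, all times 28 days, true HR 2.0.*

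| Recovered by week 4 (assumed) | Exact times | Breslow | Efron | Complementary log-log on status |
|---|---|---|---|---|
| 30% | 2.01 | 1.70 | 1.95 | 2.02 |
| 50% | 2.02 | 1.52 | 1.83 | 2.02 |
| 70% | 2.02 | 1.34 | 1.65 | 2.04 |
| 85% | 1.99 | 1.18 | 1.43 | 2.03 |

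With a true HR of 1.5, Breslow gives 1.31 and 1.21, and Efron 1.46 and 1.40, at 50% and 70% recovered.

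**Why Breslow behaves this way.** With one tied risk set and m recovered, the log partial likelihood is m × [β × (mean of x among the recovered) − log(sum of exp(βx) over all patients)]. For standard-normal x the second term is β²/2 plus a constant, so the estimate is simply the mean of x among the recovered. Computed directly for a true HR of 2.0, that mean is 0.527, 0.411, 0.283 and 0.169 at the four recovery shares. Exponentiated, this gives 1.69, 1.51, 1.33 and 1.18, matching the simulation. As everyone recovers, the estimate goes to zero whatever the true effect.

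**Standard errors.** Let V be the variance of x and p = m/n. For a predictor with no effect, the Breslow information is mV, but the score has variance of about mV(1 − p), because the recovered are drawn without replacement from the same 200. Hence model SE / true SD = 1/√(1 − p).

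- p = 0.5: 1/√0.5 = 1.41. The 1.96 cut-off acts as 1.96 × 1.41 = 2.77, so the test rejects about 0.6% of the time.
- p = 0.7: 1/√0.3 = 1.83. The cut-off acts as 3.58, so the test rejects about 0.03% of the time.

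The simulated rejection rates were 0 to 1% against a nominal 5%.

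*Clock 2: time from onset, delay uniform on 0 to 90 days plus 28 days, Breslow ties.*

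- Delay unrelated to the predictor, true HR 2.0: 1.71, 1.52, 1.35 and 1.19 at 30, 50, 70 and 85% recovered. This is attenuation only.
- Predictor with no effect (true HR 1.0) but correlated with delay, 50 to 70% recovered: correlation 0.2 gives HR 0.83 to 0.84 with 40 to 56% false positives; 0.3 gives 0.74 to 0.75 with 78 to 92%; 0.5 gives 0.57 to 0.58 with about 100%.
- True HR 2.0, 70% recovered: a correlation of +0.3 gives 0.99 and −0.3 gives 1.82.

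**Models that need no event times.** Complementary log-log regression on day-28 status returns 2.02 to 2.04 for a true HR of 2.0. Logistic regression gives odds ratios of 2.40 to 4.18 on the same data. These are valid, but on a different scale from the HR.

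**If weekly dates existed.** Cox with weekly times and Breslow ties gives 1.92, 1.85, 1.74 and 1.59 at 30, 50, 70 and 85% recovered. Attenuation is smaller but still present.

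**The case against.** The strongest reply is that the article never says outcome is read only twice. It is a condensed account, its flow chart is not available here, and a visit schedule, event definition and censoring rule may stand in the full protocol. Patients attend 20 sessions, so serial dated readings are feasible. The Abstract and section 3.2 speak of following the evolution of the paralysis. Section 2.7 also does not say whether before and after refers to the course or to a session. This stands as a limit: a reader might infer that the trial has no event times at all, and the document does not establish that. What it does establish is that the readings it describes do not fit the model it names. A later analysis plan can define an event, but it cannot recover event times from one post-treatment reading.

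Three other stronger readings go too far:

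- **That the hazard ratios will reflect enrolment delay.** This needs an onset clock and a predictor related to delay. The article states neither.
- **That the model is circular because Table 4 links Pr near 1 to better prognosis.** No section defines the event by Pr, so this is a risk to exclude, not an error made.
- **That the bias is as large as the gap between a Cox coefficient and a log odds ratio.** Those are different scales, and the comparison overstates the loss. The figures above compare hazard ratio with hazard ratio.

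It is also fair to say that section 2.9 gives H-B its own rank-type analysis, so the ordinal data are not ignored overall, and that the prognostic model is only one part of the project.

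**Conclusion.** The concern holds for the plan as described. A time-to-event model is paired with readings before and after a course of common length, and those readings carry no patient-specific event times.

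On the treatment-start clock, a true HR of 2.0 per SD shows as about 1.7 to 1.2 (Breslow) or 1.9 to 1.4 (Efron) as assumed recovery rises from 30 to 85%. Breslow standard errors are too wide, by a factor of about 1.4 at 50% recovery for a predictor with no effect. The loss is small when few recover and Efron ties are used (1.95 at 30%). On the onset clock the effect is attenuated to a similar degree, and it is biased in either direction if the predictor is related to delay.

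The direction of the attenuation follows from the design described. Its size rests on the assumed recovery share, tie method and delay correlation. The conclusion would change if dated serial assessments exist outside the article.

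**What to change.** In 2.9 and 3.2, replace Cox regression with a model of end-of-treatment H-B status: proportional-odds regression on the grade, or logistic or complementary log-log regression if a binary recovered category is defined. Use baseline predictors, including Pr, H-B, blink reflex and days since onset. Define the outcome by H-B and not by Pr. Keep the planned cross-validation, and limit the prognostic claim to status at 4 weeks.

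If the full protocol does contain dated serial assessments, a time-to-event analysis may stay, but as a discrete-time or interval-censored model, with the event, time origin and assessment dates stated.

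The cost is a change of wording; the article already lists these measurements, and days since onset follows from the course of disease checked at entry. The real downside is that the claim narrows from the development and prognosis of the paralysis to its status at 4 weeks.

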## Results

3

### Research on automatic extraction and visual analysis method of interested region based on deep learning

3.1

Based on the image segmentation framework of convolutional neural networks (CNN, one of the most commonly used deep learning models), a local image block centered on a pixel is taken as a processing object, and a method for segmenting a facial image of a patient with FP is implemented by pixel-by-pixel classification. The basic steps are as follows. Above all, the experts manually segment the region of interest on the face image to obtain the segmented image of gold standard and initially identify 100 images. Subsequently, the experts extract training samples, which are the local image block in face images. Researchers select some pixels from the region of interest, and use these pixels as the center to extract local image blocks as positive samples, the same, extract local image blocks from other regions as negative samples. Training sample set is represented as $\text{X}=\left\{\left({\text{x}}_{1},y_{1}\right)|\text{i}=\text{1,2,}\cdots \text{m}\right\}$, ${\text{X}}_{1}\in {\text{R}}^{\omega \times \omega \times \text{h}}$(ω×ω: the size of local image block, h=3: the number of image channels) stands for the local image block, ${\text{y}}_{\text{i}}\in \{0,1\}$ (1: interested region, 0: noninterested region) means image block marking. Thirdly, rotating, translating, shearing, and symmetrical flipping are performed on local image block samples to enlarge the sample capacity and prevent the overfitting of CNN to a certain extent, and then CNN network including convolutional layer, pooling layer, fully connected layer, and Softmax classification loss layer is set up. During the process of building CNN network, a linear correction unit ReLU activation function (f(x)=max(0,x)) is added after the combination of each convolutional layer and pooling layer, improving the training speed and accuracy, and the Softmax classification loss layer defines the objective function of the CNN network $1(\text{X,C})=-\frac{\log{\text{e}}^{{\text{X}}_{\text{C}}}}{\sum_{\text{k}=1}^{\text{C}}{\text{e}}^{\text{Xk}}}$ (x: training data, c: data category). At last, the CNN network is trained using back propagation algorithm (BP). Combining all the above steps, the overall operation process is that, when a new test image is input, with each pixel of the test image as the center, the extracted local image blocks are input into the trained CNN network, the output is the probability value that the central pixel belongs to each category, and the pixels are classified according to the magnitude of the probability value.

### Establishment of predictive model for prognosis of FP based on LASCA technology and research on rehabilitation training mechanism

3.2

The researchers automatically segregate 3 areas of the eyelid, cheek, and jaw of the affected and healthy side of the patient's facial blood flow image are by machine learning methods and synchronize them. At the same time, the common FP assessment method is incorporated into a unified mathematical statistical model, and the law of change in LASCA symmetry value Pr and the development, evolution, and prognosis of FP is observed. The relevant characteristic signals are extracted, and a COX regression analysis method was adopted to establish a highly accurate prediction model for the prognosis of FP based on LASCA technology, and cross-validation is performed.

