**Results::**

The standard image of the facial target area with facial nerve injury will be manually segmented by the convolutional neural network method. The blood flow images of the eyelid, cheek, and mandible of the patients’ affected and healthy side will be compared and evaluated. Laser speckle blood flow symmetry Pr and its changes in FP condition evolution and prognosis outcome will be measured, and relevant characteristic signals values will be extracted. Finally, COX regression analysis method is conducted to establish a higher accuracy prediction model of FP with cross-validation based on laser speckle blood flow imaging technology.

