At present, the clinical evaluations of facial nerve function after FP are mainly based on scales, of which House-Brakmann (H-B) rating scale is the most widely used. Although H-B rating scale has no specific and clear quantitative indicators to describe the severity of facial nerve injury, resulting in deficiencies in utility and reliability.^[4,5]^ In addition, the objective diagnostic indexes of PFP are neuroelectrophysiological diagnostic tests including surface electromyogram (EGM), nerve excitability measurement, facial nerve electrogram, EGM (the criterion standard for judging the prognosis and efficacy of facial nerves), blink reflex (BR, the most sensitive index for early diagnosis of FP to directly or indirectly reflect facial nerve conduction function) and F wave. Unfortunately, in clinical practice, EGM alone cannot reflect the degree of inhibition, damage and degeneration of the electrical conduction of the nerve, especially the low positive rate of detecting mild-to-moderate FP, besides, the facial nerve function cannot be evaluated in the acute stage of the lesion, making the detection lagging. BR requires professional operation, and the process is complicated, causing pain and discomfort to the patient, resulting in poor patient acceptance.^[6]^ Electrophysiological testing cannot dynamically reflect the evolution of FP but only shows the facial nerve function currently being examined. It is difficult to provide effective objective assessment of acupuncture for FP.

Facial nerve compression of FP is mainly caused by local neurotrophic vasospasm and tissue edema due to inflammation, edema, ischemia, or autonomic nervous system disorder in the facial neural canal and surrounding tissues.^[7]^ Some in-depth researches believed that facial nerve ischemia in patients with FP can lead to different degrees of blood circulation disorders, and its recovery depends on stable internal neurological environment and nutritional supply, which are based on good blood circulation.^[8,9]^ A comprehensive understanding of the blood circulation of the facial nerve can help evaluate the development and prognosis of PFP; thus, a new method for evaluating FP was proposed based on the dynamic observation of local conditions of PFP using infrared thermal imaging.^[10,11]^ Nevertheless, infrared thermal imaging has high environmental requirements, blurred imaging, poor experimental consistency, and insurmountable technical defects.^[12]^

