### Design

2.1

This study is an observational trial conducted in Shenzhen Hospital of Traditional Chinese Medicine, China. After getting written informed consent, H-B scale, BR, facial structure symmetry analysis, and LASCA technique testing were performed on 200 eligible patients with PFP. The primary objective is to provide a new visual and objective evaluation method for studying the mechanism and efficacy of acupuncture treatment of FP and develop an interactive augmented reality facial nerve function rehabilitation training system with multiple training modes. The study flow chart is showed in Figure 1.

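### The prognostic model is claimed to be accurate with no stated comparator, so its cross-validated accuracy cannot by itself show that LASCA predicts better than H-B and BR

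*Protocol article*

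**What the plan says.** Section 3.2 of the protocol article states that "the common FP assessment method is incorporated into a unified mathematical statistical model" and that Pr is observed against the course and prognosis of facial paralysis. Its next sentence says that characteristic signals are extracted and Cox regression is used to "establish a highly accurate prediction model for the prognosis of FP based on LASCA technology, and cross-validation is performed". The Results paragraph of the abstract describes the same step as a way to "establish a higher accuracy prediction model of FP with cross-validation based on laser speckle blood flow imaging technology". Neither place names a model against which accuracy is to be judged.

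Section 3.2 does not list the common assessments. The rest of the article identifies them well enough. The Introduction says that the "House-Brakmann (H-B) rating scale is the most widely used". Section 2.1 says that "H-B scale, BR, facial structure symmetry analysis, and LASCA technique testing were performed on 200 eligible patients with PFP". Section 2.9 says: "The correlation between H-B score, BR, and Pr would be analyzed by correlation analysis".

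The other analyses in section 2.9 are Ridit analysis of H-B, a paired t test on Pr before and after treatment, and Cox regression for the course and prognosis. None compares prediction with and without Pr.

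**The concern.** The article's case for LASCA is comparative. The Introduction argues that the H-B scale and electrophysiology fall short and that a new objective measure is needed. For prognosis, the question that follows is whether Pr tells the clinician something that H-B and BR do not.

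The overall accuracy of one model does not answer that. Cross-validation corrects a model's accuracy for optimism; it does not divide that accuracy among the predictors. If severity measures sit in the model, they can supply the accuracy. If Pr stands alone, it can predict because it tracks severity. At stake is whether a good C-index may be reported as evidence for LASCA.

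**Working it through.** **No plan figure to reproduce.** The article gives no C-index, event count, effect size or power for the prognostic model. Its one design figure, 200 patients, comes without the inputs needed to recompute it.

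**Two readings of section 3.2.**
- *Pooled:* H-B, BR and Pr are all predictors. The reported accuracy is that of the set.
- *LASCA only:* the Cox predictors are Pr and other LASCA signals. The reported accuracy is that of Pr, including whatever it shares with severity.

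**Are existing tests likely to be prognostic?** The Introduction calls EMG "the criterion standard for judging the prognosis and efficacy of facial nerves". That phrase concerns EMG, not H-B or BR, so it makes prognostic value of the common assessments plausible without establishing it. The effect is therefore varied below, including no effect.

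**Illustrative Cox simulation.** Only N = 200 is from the article; all other settings are assumptions.
- H-B is standard normal; BR = 0.5 × H-B + √0.75 × noise.
- Pr = ρ × H-B + √(1 − ρ²) × noise, with ρ = 0 or 0.5.
- Hazard = exp(β_H × H-B + β_B × BR + β_P × Pr), with β = log(HR per SD) and β_H = β_B.
- Follow-up is cut so that 75% of patients have the event; 5-fold cross-validation; 150 replicates.
- C-index = share of comparable pairs in which the patient with the earlier event has the higher predicted hazard, ties counting one half.

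Mean cross-validated C-index:

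| HR per SD (H-B and BR each) | Pr | H-B + BR | H-B + BR + Pr | Pr alone |
|---|---|---|---|---|
| 1.0 | no effect, ρ = 0 | 0.500 | 0.504 | 0.501 |
| 1.25 | no effect, ρ = 0 | 0.600 | 0.599 | 0.498 |
| 1.5 | no effect, ρ = 0 | 0.673 | 0.671 | 0.500 |
| 2.0 | no effect, ρ = 0 | 0.757 | 0.756 | 0.507 |
| 1.0 | no own effect, ρ = 0.5 | 0.503 | 0.501 | 0.498 |
| 1.25 | no own effect, ρ = 0.5 | 0.601 | 0.598 | 0.543 |
| 1.5 | no own effect, ρ = 0.5 | 0.673 | 0.671 | 0.574 |
| 2.0 | no own effect, ρ = 0.5 | 0.755 | 0.754 | 0.602 |
| 1.5 | HR 1.5 per SD, ρ = 0 | 0.663 | 0.689 | 0.592 |

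*Pooled reading.* With H-B and BR at HR 1.5, the pooled C-index is 0.671 when Pr adds nothing and 0.689 when Pr has HR 1.5. Seen alone, neither value reveals which case holds. The differences do: 0.671 − 0.673 = −0.002 against 0.689 − 0.663 = +0.026. Across all eight rows where Pr adds nothing, the difference never exceeds 0.004 in size.

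*LASCA-only reading.* At the same HR of 1.5, Pr alone gives 0.574 when it only tracks H-B and 0.592 when it is truly prognostic. The accuracy of Pr alone barely separates the two. The planned correlation of Pr with H-B and BR would show the overlap, not the added value.

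**Second illustration, logistic stand-in.** N = 200, 300 datasets per effect size, H-B uniform on grades II to VI, BR correlated 0.5 with H-B, three Pr variables of pure noise, recovery depending on H-B only. At assumed log odds ratios of 0.5 / 0.8 / 1.1 per SD of H-B, the mean 10-fold cross-validated AUC of the pooled model was 0.60 / 0.68 / 0.75. A likelihood-ratio test of Pr given H-B and BR rejected in 3% / 4% / 7% of datasets, close to the nominal 5%. The test for added value thus behaves properly where overall accuracy misleads.

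**The case against.** A reader might infer more than the text supports: that the model will look accurate whatever Pr does, and that its result can say nothing about LASCA. The case against that reading is strong.

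- **Pooling is an inference.** The unified model and the Cox model appear in separate sentences of section 3.2, and the abstract names no common assessment as a predictor. H-B, assessed before and after acupuncture under section 2.7, might even serve as the outcome.
- **A pooled fit does carry information on Pr.** Cox output includes a coefficient and P value for Pr adjusted for H-B and BR; for one Pr term, that test is asymptotically equivalent to the likelihood-ratio test.
- **There is no decision rule.** The article does not say that LASCA succeeds if the AUC exceeds some value. Nor is an AUC of 0.60 highly accurate.
- **The article condenses a fuller document.** A covariate list or benchmark model may stand in a full protocol or SAP that is not shown, and the accuracy wording may be loose English.

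The first three stand and rule out the stronger reading. The fourth stands only in part: a missing covariate list is no finding, but the accuracy claim and its credit to LASCA are in the article. The choice of reading does not rescue that claim, because neither model's overall accuracy is a comparison with H-B and BR. If H-B after treatment were the outcome, H-B before treatment would still be available as a base predictor.

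**Conclusion.** The point holds in a limited form. The article promises an accurate prognostic model based on LASCA and states no comparator. On either reading, overall cross-validated accuracy does not show that Pr improves on assessments already in use.

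The size is illustrative. Under assumed hazard ratios of 1.25 to 2.0 per SD for H-B and BR, a pooled model reaches about 0.60 to 0.76 with a Pr that adds nothing. A Pr that merely correlates 0.5 with H-B reaches about 0.54 to 0.60 alone. These values depend on the assumed effects, correlations and 75% event share. If the common assessments are not prognostic, the pooled model stays near 0.50 and would not look accurate. The accuracy *can* therefore come from elsewhere; the documents do not show that it will.

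This deserves correction before analysis because it changes what may be concluded about LASCA. It does not invalidate the data collection or the other analyses.

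**What to change.** In sections 2.9 and 3.2, name two nested Cox models for the same endpoint, fitted in the same cross-validation folds:

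1. baseline H-B and BR;
2. the same plus baseline Pr, as one term or as several regional terms.

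Base the statement on LASCA's prognostic value on the likelihood-ratio test for Pr (joint if there are several terms) and on the cross-validated difference in C-index with its confidence interval. The overall C-index of each model can still be reported as description. In the abstract and section 3.2, replace the accuracy claims with the question whether Pr adds accuracy beyond H-B and BR.

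The cost is one further model fit and a few words of text, on variables already collected. The drawback for the sponsor is that the reported gain from LASCA will be smaller than the overall accuracy.
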